# Study protocol: a randomized, double-blind, parallel, two-arm, placebo control trial investigating the feasibility and safety of immunoglobulin treatment in COPD patients for prevention of frequent recurrent exacerbations

**DOI:** 10.1186/s40814-018-0327-z

**Published:** 2018-08-11

**Keywords:** Immunoglobulin, COPD, COPD exacerbation, Pilot study, Randomized clinical trial, Feasibility and safety

## Abstract

**Background:**

Chronic obstructive pulmonary disease (COPD) is a chronic progressive inflammatory disease of the airways, associated with frailty, disability, co-morbidity, and mortality. Individuals with COPD experience increased risk and rates of acute exacerbation as their lung disease worsens. Current treatments to prevent acute exacerbation of COPD (AECOPD) are only modestly effective. New therapies are needed to improve the quality of life and clinical outcomes for individuals living with COPD and especially for those prone to frequent recurrent AECOPD. Recent research has suggested an association of gammaglobulin or immunoglobulin G levels with AECOPD and a favorable effect of an immunoglobulin treatment on the frequency of recurrent AECOPD, healthcare provider visits, treatments, and hospitalizations. However, control trials are required to confirm this apparent association and therapeutic effect. This study aims to assess if intravenous immunoglobulin (IVIG) therapy is feasible, safe, tolerable, and potentially effective in reducing the frequency of recurrent AECOPD.

**Methods/design:**

Adult COPD patients at The Ottawa Hospital (TOH) will be recruited to partake in a randomized double-blind, parallel, two-arm, placebo control trial. Eligible patients will be administered either IVIG or normal saline following 1:1 randomization and every 4 weeks for 1 year. The primary outcome of feasibility will be determined by recruitment, patient adherence, safety and tolerance, success of the follow-up procedures, and outcome measurement. The safety and tolerability will be assessed through adverse events, adherence, and study withdrawals. Efficacy trends will be investigated by assessing incidence rates of AECOPD, improvement in quality of life, and healthcare services use and cost.

**Discussion:**

The study results will inform larger studies designed to confirm a clinically significant therapeutic effect in identifiable populations which would be a major advance in the care of COPD patients.

**Trial registration number:**

ClinicalTrial.gov, NCT03018652 and NCT02690038.

**Electronic supplementary material:**

The online version of this article (10.1186/s40814-018-0327-z) contains supplementary material, which is available to authorized users.

## Background

Chronic obstructive pulmonary disease (COPD) is a chronic respiratory disease characterized by a progressive decline in lung function, shortness of breath, exercise limitation, poor health status, and increased mortality. The World Health Organization cites COPD as the third leading cause of death worldwide and estimates that it affects 65 million people [1]. COPD is a leading cause for hospital admission and readmission in North America and is thought to cost the Canadian healthcare system more than 700 million dollars annually [2].

Patients with COPD experience episodic flares of their disease. Clinically, these acute exacerbations of COPD (AECOPD) are characterized by increased cough, shortness of breath, sputum production, weakness, and worsening airflow obstruction [3]. Pathologically, AECOPD correlate with a high degree of systemic inflammation and immune system activation. As COPD severity worsens, the frequency of exacerbations increases [4]. AECOPD likely increases the progression of COPD, and additionally, it is likely that the inflammatory milieu created by AECOPD increases susceptibility to additional, recurrent AECOPD [4].

AECOPD have a significant impact on individual well-being and the healthcare system. Previous studies have shown that patients with exacerbations experience reductions in quality of life such as the ability to engage in activities of daily living, a worsening of lung function, and an increased risk for mortality both during and after the acute exacerbation period [5]. Moreover, exacerbation events often cause the patient to seek acute medical attention and admission to hospital, which drives the large healthcare costs [6]. History of hospital admission due to AECOPD is the strongest risk factor for readmission for recurrent AECOPD within 1 year [7, 8]. Hospitalization for AECOPD is also associated with lower 3-year survival as compared to COPD patients without a history of hospitalization in the previous 3 years, independent of the severity of airflow limitation [7]. As a result, reducing exacerbations has been a strong focus of research, with potential direct positive impacts to patients and the healthcare system.

Unfortunately, there is no cure for COPD, and highly effective therapies are currently lacking. The current Global Initiative for Chronic Obstructive Lung Disease (GOLD) guidelines recommend smoking cessation, exercise training, maximal bronchodilator therapy, and influenza and pneumococcal vaccinations to prevent exacerbations [9]. In patients with frequent exacerbations, chronic macrolide therapy with azithromycin [10], *N*-acetylcysteine [11], and roflumilast (a phosphodiesterase-4 inhibitor) [12] have been shown to increase the time to recurrent exacerbation. However, these therapies are only modestly effective, and patients continue to experience exacerbations while on maximal therapy. Further research into new therapeutics to prevent and reduce exacerbations is imperative. The development of newer immunomodulatory agents as adjuvant therapy to prevent AECOPD has become an area of intense investigation [13, 14].

Patients with COPD have lower immunoglobulin G (IgG) levels than patients with other lung diseases independent of oral steroid use and age [15]. Moreover, lower baseline serum IgG or gammaglobulin levels are correlated with higher rates of AECOPD [16, 17], but recurrent AECOPD still occur despite having normal baseline serum IgG as well [16]. There is no evidence of a threshold level of gammaglobulin or IgG to predict recurrent AECOPD risk, it rather appears to be a continuous, or linear relationship that extends into the “normal” range of immunoglublin G levels. From the evidence of association, it is possible that both the exacerbator phenotype and treatment cause low levels and that low levels cause a recurrent exacerbation. Neither suggests whether immunoglobulin treatment may or may not offer benefit.

Immunoglobulin for intravenous and subcutaneous infusion (IVIG and SCIG) is prepared from pooled plasma from thousands of healthy blood or plasma donors. The large donor pool ensures a diversity of antibody specificities to a wide spectrum of antigens and microbial pathogens [18]. Immunoglobulin for transfusion represents a privileged source of natural antibodies (NAb) that occur in the absence of autoimmune disease or immunization. NAb are not only an immune defense against pathogens [19, 20] but also have anti-inflammatory and immunomodulatory activities [21, 22]. Given the heightened systemic and airway inflammation in COPD, propensity for infection-triggered AECOPD, and suppressed mucosal or systemic immunity [23, 24], the anti-inflammatory, anti-infective, and immunomodulatory effects of Ig preparations could also be beneficial in this group.

We recently reported a retrospective, single-center, case series of Ig treatment as adjunctive preventative treatment for AECOPD in 14 patients [25]. Half (eight patients) had at least severe COPD by GOLD criteria. Ig treatment significantly reduced average moderate and severe AECOPD from 4.7 ± 3.1 to 0.6 ± 1.0 episodes per patient-year. Number of hospitalizations was markedly reduced from 12 in the year prior to 1 in the year following Ig treatment initiation [25]. Even though the median baseline IgG level in this study cohort was 5.9 g/L (interquartile range 4.1–7.4), and 36% had IgG less than 5 g/L, the apparent effect of Ig treatment in reducing moderate and severe AECOPD was consistent across levels of IgG. This similar effect was also demonstrated by another group in patients with demonstrated immunodeficiencies (mostly specific antibody deficiency) [26]. While this demonstrates some promise, prospective controlled studies are required to determine if Ig treatment could have any impact on the frequency of AECOPD in general. To ensure a successful definitive efficacy trial, we will perform a feasibility study to identify potential barriers and areas for improvement in conducting the study from the start to the end of the trial. We will also come up with an effect size estimate that can be used to calculate the sample size for the definitive efficacy trial.

This paper presents the rationale and describes the protocol for a pilot randomized control trial investigating the feasibility of immunoglobulin treatment in patients with a history of frequent recurrent AECOPD, or with a high risk of recurrent AECOPD. This study aims to determine if immunoglobulin treatment is safe, tolerable, and potentially effective in reducing the frequency of acute exacerbations. An effort in design will be to explore differences according to AECOPD history, underlying hypogammaglobulinemia, and comorbidity of bronchiectasis among the baseline characteristics. An effort in execution will be to draw patients from different settings, including inpatients, emergency department (ED) arrivals, and outpatients. If this study is feasible, it will inform larger studies to confirm the therapeutic effect of immunoglobulin treatment and would be a major advance in the care of COPD patients.

## Methods/design

### Study design, setting, and participants

The study design will be a pilot randomized double-blind, parallel, two-arm, placebo control trial, conducted at the clinical investigation unit (CIU) of the Ottawa Hospital Research Institute (OHRI), which is a research institute embedded in The Ottawa Hospital (TOH). TOH is an acute care university teaching hospital with over 1000 inpatient beds. We will recruit hospitalized, ED patients and outpatients with AECOPD. Due to the differences in the inclusion criteria, treating and recruiting staff, and dosing, administratively distinct protocols will be used for in- and outpatients and among inpatients for those with and without hypogammaglobulinemia. Outpatients will be identified for recruitment within the respiratory ambulatory care clinics, and hospitalized patients will be identified within the ED, and by screening patients admitted under general internal medicine or respiratory services. Patients who have provided permission to be contacted by a clinical research personnel will be approached to participate in the trial. If the participant agrees to participate in the trial by signing the consent form, screening for eligibility will commence. If no lung function testing was documented within the last 12 months, lung volume (forced expiratory volume at 1 s (FEV1) and forced vital capacity (FVC)) will be measured by a hand-held spirometer at the bedside. Blood tests and urinalysis will be sent to determine eligibility. A screening log for patients will be kept to identify the areas of improvement to enhance recruitment in future trials.

Eligible patients must be over 40 years old, have a confirmed diagnosis of COPD with a post-bronchodilator FEV1/FVC ratio of < 0.7 by spirometry within the previous 12 months, have a > 10 pack-year smoking history, and must be expected to live at least 12 months. Inpatients must have previously either visited the ED (moderate AECOPD) or been hospitalized for AECOPD (severe AECOPD). Outpatients must have a history of at least one exacerbation requiring hospitalization (severe AECOPD) or two exacerbations treated as an outpatient (moderated AECOPD) within the previous 12 months. Patients will be excluded from the study if any of the following criteria are met: known hypersensitivity to immunoglobulin product, active malignancy, transplant recipient, on immunomodulating or immunosuppressive agents apart from a short course of prednisone for AECOPD, primary antibody deficiency in need of immunoglobulin therapy, IgA deficiency (IgA < 0.1 g/L), nephrotic syndrome, currently on IVIG or SCIG, or current pregnancy.

### Interventions

Random 1:1 allocation will be stratified by outpatient or inpatient groups and further by baseline IgG < 7 g/L or IgG ≥ 7 g/L. In the outpatient group, the treatment arm will receive doses of 0.5 g/kg, and the control arm will receive normal saline at 5 mL/kg. Doses of IVIG and normal saline will be administered to the respective patient populations on the day of randomization and then every 4 ± 1 weeks for 44 weeks (total of 48 weeks). In the inpatient group with low baseline IgG, the treatment arm will receive doses of 0.8 g/kg, and the control arm will receive normal saline at 8 mL/kg. Treatment arm of inpatients with normal IgG levels will receive doses of 0.5 g/kg, and the control arm will receive normal saline at 5 mL/kg. A maximum dose of 80 g/dose of IVIG 10% (Gamunex or CBS IGIV-nex or Privigen or Octagam depending on availability at the blood bank) will be given to patients randomized to treatment arms. Consistent IVIG brand or formulation is routinely maintained for individual patients according to the first dose received and for subsequent doses. For control patients, normal saline will consist of 0.9% NaCl, and a maximum dose of 800 mL will be given.

For all patients, respective doses of IVIG and normal saline will be administered over an infusion time of 4–6 h by a nurse in the CIU. Doses will be determined based on patient’s weight at the time of enrolment and will be consistent throughout the study unless there is a change in weight of at least 10%, in which case, the dose will be adjusted to the new body weight. All patients will continue to receive standard treatment for COPD as directed by their regular treating physician.

Participants may withdraw from the study at any time and for any reason; however, they will be encouraged to stay on their assigned study medications in the absence of illness- or treatment-related adverse events. All patients will be followed up for adverse events and outcomes for 1 year from randomization. The sponsor (OHRI), the qualified investigator, or a treating physician may withdraw the participant at their discretion or in the event of intercurrent illness, intolerance to the study treatment, adverse events, pregnancy, protocol violation, or administrative reasons. All participants discontinued due to an adverse event will be followed until the event resolves or becomes chronic or stable. Appropriate medical care will be provided until signs and symptoms have remitted or stabilized or until abnormal laboratory findings have returned to acceptable or pre-study limits.

After the study completion, patients will continue their clinical care with their primary care provider or specialist, as prior to and during the study period. Patients may elect to stay on IVIG treatment by prescription according to the judgment of the treating physician.

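### Among treated inpatients the IgG stratum fixes the IVIG dose, so IgG differences there are IgG and dose combined, and the by-arm safety summary mixes two doses

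*Protocol article*

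**What the plan says.** Everything about dose stands in the protocol article under Interventions.

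- Allocation: "Random 1:1 allocation will be stratified by outpatient or inpatient groups and further by baseline IgG", with the cut at 7 g/L.
- Inpatients with low IgG: "In the inpatient group with low baseline IgG, the treatment arm will receive doses of 0.8 g/kg", with saline controls at 8 mL/kg.
- Inpatients with normal IgG: "Treatment arm of inpatients with normal IgG levels will receive doses of 0.5 g/kg", with saline controls at 5 mL/kg.
- Outpatients: 0.5 g/kg or 5 mL/kg saline, whatever their IgG.
- Caps: 80 g of a 10% product for IVIG; for saline, "a maximum dose of 800 mL will be given".

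The dosing paragraph speaks of low and normal IgG without repeating the cut. I read these terms as the 7 g/L strata.

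Two other places matter. The Background says that the design will try to "explore differences according to AECOPD history, underlying hypogammaglobulinemia, and comorbidity of bronchiectasis", and the sentence goes on to place these among the baseline characteristics. Under Data collection, management, and analysis, adverse events and tolerability are to be summarised with point estimates and 95% confidence intervals for the intervention and control groups. No breakdown by dose is stated, and none is ruled out. The section on design, setting and participants gives dosing as one reason for administratively separate protocols, but draws no consequence for interpretation.

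**The concern.** No inpatient with low IgG is assigned 0.5 g/kg, and no inpatient with normal IgG is assigned 0.8 g/kg. Within the treated inpatients, IgG stratum and nominal dose are the same variable. If low-IgG inpatients on IVIG have more adverse events, or fewer exacerbations, the difference could be put down to IgG status when dose would explain it equally well. Inpatients are 48 of the 64 planned patients, so most of the information on IgG status carries this ambiguity.

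Safety and tolerability are named secondary outcomes, and the pilot is meant to inform a larger trial that will have to choose a dose. A by-arm estimate describes a mixture whose weights depend on how many low-IgG inpatients happen to be recruited. It does not say what to expect at 0.8 g/kg or at 0.5 g/kg.

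**Working it through.** **1. The plan's own volumes.** A 10% product contains 1 g per 10 mL. So 0.8 g/kg × 10 = 8 mL/kg, 0.5 g/kg × 10 = 5 mL/kg, and 80 g × 10 = 800 mL. The saline volumes and the saline cap match the IVIG volumes exactly within each stratum.

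**2. Dose ratio between the inpatient IgG strata.** At weight w the ratio is min(0.8w, 80) / min(0.5w, 80). The cap is reached at 80/0.8 = 100 kg in the low-IgG stratum and at 80/0.5 = 160 kg in the normal-IgG stratum.

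| Weight (kg) | Low IgG (g) | Normal IgG (g) | Ratio |
|---|---|---|---|
| 70 | 56 | 35 | 1.60 |
| 100 | 80 | 50 | 1.60 |
| 110 | 80 | 55 | 1.45 |
| 120 | 80 | 60 | 1.33 |
| 140 | 80 | 70 | 1.14 |
| 160 | 80 | 80 | 1.00 |

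Volume follows the same ratio. The article gives no weight distribution.

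**3. What each contrast identifies.** Cross IgG stratum with dose for treated inpatients. Of the four cells, the plan fills two: low IgG at 0.8 g/kg and normal IgG at 0.5 g/kg.

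- IVIG minus saline within a stratum: randomised and volume-matched, so valid for that stratum at its dose.
- Low-IgG effect minus normal-IgG effect: one observed difference that contains both the change in IgG and the change in dose. Without the two empty cells it cannot be split.
- IVIG minus saline over all strata: valid for the policy of dosing by setting and IgG, as assigned.

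Outpatients all have the same nominal dose per kg, so their IgG contrast is free of the dose problem. However, only about 16/2 = 8 of them are treated.

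**4. How many patients are on each regimen.** At 1:1, 64/2 = 32 patients receive IVIG, and 48/2 = 24 of them are inpatients. The share of inpatients below 7 g/L is not given. The only IgG distribution in the document is from the retrospective series of 14 Ig-treated patients cited in the Background: median 5.9 g/L and upper quartile 7.4 g/L. Since 5.9 < 7 < 7.4, between 50% and 75% of that series lay below 7 g/L. It is a small, selected group, so I use this as an assumption and add 25% as a lower case.

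| Low-IgG share | On 0.8 g/kg | On 0.5 g/kg | Share of arm on 0.8 | Mean nominal dose (g/kg) |
|---|---|---|---|---|
| 25% | 6 | 26 | 18.8% | 0.56 |
| 50% | 12 | 20 | 37.5% | 0.61 |
| 75% | 18 | 14 | 56.3% | 0.67 |

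The mean is (0.8 × n at 0.8 + 0.5 × n at 0.5)/32. For the 50% case this is (9.6 + 10)/32 = 0.6125.

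**5. What mixing does to an event rate (invented rates, for illustration only).** Suppose 40% of patients have a given adverse event at 0.8 g/kg and 20% at 0.5 g/kg. With 12 and 20 patients, the arm estimate is (0.40 × 12 + 0.20 × 20)/32 = 8.8/32 = 27.5%, which is the rate of neither regimen.

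**The case against.** The strongest reply is that this belongs to the analysis plan. A breakdown of adverse events by stratum is commonly left to that document, which is not shown, and the article does not exclude one. The groups already have their own protocols, strata and volume-matched controls, so the design supports the comparison asked for. No low- versus normal-IgG test is specified, and the Background sentence is a statement of intent about baseline factors. Most efficacy measures are to be described only, in a pilot whose primary outcome is feasibility. Dosing by IgG is a legitimate treatment policy, and since IgG is not randomised, a difference between strata would not be a pure IgG effect even at equal doses.

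Much of this stands, and it keeps the point small. It does not remove it. The overlap of IgG and dose is fixed by the dosing rule, and no table can undo it, so the limit on interpretation holds whatever the analysis plan says. The safety reporting unit that the article does state is the arm.

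A reader might infer more than the document supports:

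- *That the treatment comparison is confounded.* It is not. Allocation is stratified and saline volume matches within each stratum.
- *That infusion rate also differs by a known factor.* Doses "will be administered over an infusion time of 4–6 h", and where in that window a patient falls is not tied to dose, so no rate ratio is fixed.
- *That a tighter confidence limit for the pooled arm than for one regimen shows harm from pooling.* It shows mainly that smaller groups give wider intervals.

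**Conclusion.** The point holds as a limit on interpretation and a cheap improvement, of low severity. It is not an error in the primary analysis. Among treated inpatients, IgG stratum carries a 1.6-fold difference in nominal dose up to 100 kg, falling to none at 160 kg, so an inpatient IgG contrast cannot be told from a dose contrast below that weight. The safety and tolerability summary, as stated by arm, gives no separate estimate for either dose.

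The size rests on two assumptions: that low and normal IgG in the dosing paragraph mean the 7 g/L strata, and that 50% to 75% of inpatients fall below that cut. On these, 12 to 18 of the 32 IVIG patients are on the higher dose, and fewer if the share is lower. The overlap of IgG and dose does not depend on the second assumption.

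**What to change.** Keep dosing and allocation as they are; which dose is right is a clinical question outside this point.

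1. Beside the pooled summary, report adverse events, tolerability and descriptive AECOPD for the 0.8 g/kg low-IgG inpatients against their own 8 mL/kg saline controls. Report the 0.5 g/kg patients against their 5 mL/kg controls separately. The second group still mixes outpatients with normal-IgG inpatients, and a footnote should say so.
2. State that any inpatient contrast between IgG strata is IgG and dose combined.

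The cost is one descriptive table and one sentence, since the groups are already defined by the randomisation strata. If the analysis plan already splits safety by stratum, only the sentence is needed.

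The downside is small cells. With 12 to 18 patients per arm at 0.8 g/kg, the exact 95% upper limit when no event is seen, 1 − 0.025^(1/n), is 26.5% for n = 12 and 18.5% for n = 18. Those intervals are wide and should be shown as such. The pilot will still not separate IgG from dose among inpatients.

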### Allocation of study treatment and blinding

Each participant will receive a unique participant identification (ID) number. The trial statistician will designate another statistician to prepare all randomization schemes. A computer-generated randomized allocation output will be given to CIU nurse in an unblinded fashion. The CIU nurse will send a request to TOH blood bank to issue IVIG product with the participant ID number on it at first and all subsequent visits. Only the blood bank staff and the CIU nurse will have knowledge of the treatment allocation. The CIU nurse will prepare IVIG or normal saline infusion kit, and these will be administered in a concealed manner. In order to minimize the selection and ascertainment biases, physicians, investigators, and research staff will be blinded to the randomization schemes and treatments administered. Unblinding should only occur under exceptional or emergency circumstances where death or life-threatening complications require knowledge of the study treatment allocation. This information will allow the investigator to make an informed decision regarding the treatment and management of the participant.

